#### 9.4.4 SAFETY ANALYSES

**Secondary safety outcomes** will be obtained via participant follow-up questionnaires performed 24, 48, and 168 hours (7 days) after enrollment (Time 0 – consent date and time).

Summaries of incidence rates (frequencies and percentages), intensity, and relationship to study of individual AEs by System Organ Class and Preferred Term (MedDRA) will be prepared. All AEs beginning after randomization but before discharge will be included. Basic summaries by assigned groups will be prepared. The DSMB may request to see more detailed tables. The occurrence of any adverse event will be considered as a dichotomous outcome.

To obtain SAE, palpitation, pre-syncope/syncope, chest pain, and arrhythmia data; each questionnaire will contain open ended, non-symptom specific questions where caregivers can provide the study team with information about their child's illness or any other concern they may have. Any response to this question will result in a trained study team member discussing the information provided in more detail via telephone. Any symptom or condition that meets the definition of an SAE will be categorized as such and reported appropriately.

1. **Frequency of diarrheal episodes during the 48-hours following ED disposition:** Frequency and maximal number of diarrheal episodes will be obtained by asked about presence of diarrhea on each questionnaire the caregiver completes. If diarrhea is present, further questions related to the number of episodes will be asked. Frequency will be calculated over 48 hours for all patients regardless of whether they have greater than 24 hours with no symptoms.
2. **Maximal number of diarrheal episodes in 24 hours:** Same as above – Frequency
3. **Serious Adverse Events (SAEs)**
4. **Palpitations**
5. **Pre-syncope /syncope**
6. **Chest Pain**

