a First dose of study intervention can be administered 8 hours after administration of clinical dose of Ondansetron (at presenting ED visit)  
b Dose of study intervention will be administered at home based on caregiver determination. The final dose should be administered within 48 hours of first clinical dose of Ondansetron. Should the caregiver administer doses of study medication >72 hours post clinical dose of Ondansetron, it will be considered a protocol deviation. We will collect dose details at each follow-up time point. Any doses administered after the 48 hour follow-up time point will be recorded on the 168 hour (Day 7) follow-up questionnaire.

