#### 6.4 STUDY INTERVENTION COMPLIANCE

After randomization and treatment assignment, the qualified research team member will complete a study medication dispensation form which contains the blinded kit number, expiration date, participant study ID, participant weight and age at time of enrollment, dose dispensed, the name and signature of the dispensing staff member, and the date and time of dispensation.

A drug accountability log will also be maintained at all participating institutions containing the initials of the qualified research team member dispensing the intervention to the participant caregiver, the kit number used, the accompanying participant study ID and date and time of dispensation.

The qualified research team member will demonstrate to the caregiver how to measure and dose the study medication. The exact volume in milliliters of the 4mg/5mL solution will be calculated by the research team member using REDCap prior to the caregiver leaving the ED.

The caregiver will be instructed to provide one dose every 8 hours to a maximum of 3 doses in a 24 hour period for 48 hours after discharge from the ED, as they feel their child requires the intervention. **The caregiver may choose to administer a minimum of zero to a maximum of six doses (excluding vomited doses) to the participant. If the caregiver does not administer any doses of the study intervention; the participant is still considered compliant with the study protocol.**

The number of doses administered to the participant by the caregiver will be recorded via telephone or email questionnaire performed 24 and 48 hours after enrollment (*Time 0 – Consent Date and Time*). Caregivers will be asked to return unused study medication and/or empty bottles to the study team or to a community pharmacy for destruction after the completion of the 7 day follow up period.

The participant will be considered not compliant with the protocol if the study team is unable to contact the caregiver/participant for the follow-up schedule as detailed in the SoA (section 1.3) to a maximum of 21 days after enrollment.

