#### 8.3.4 TIME PERIOD AND FREQUENCY FOR EVENT ASSESSMENT AND FOLLOW-UP

The occurrence of an adverse event (AE) or serious adverse event (SAE) may come to the attention of study personnel during the follow-up questionnaires performed with caregivers or if a study participant presents for medical care to the enrolling ED, or upon review of data by a study monitor.

All AEs including local and systemic reactions not meeting the criteria for SAEs will be captured on the appropriate case report form (CRF). Information to be collected includes an event description, date and time of onset, clinician's assessment of severity, relationship to study product (assessed only by those with the training and authority to make a diagnosis), and date and time of resolution/stabilization of the event.

Any medical condition that is present at the time the participant is screened will be considered as baseline and not reported as an AE. However, if the study participant's condition deteriorates at any time during the study, it will be recorded as an AE.

Changes in the severity of an AE will be documented to allow an assessment of the duration of the event at each level of severity to be performed. AEs characterized as intermittent require documentation of onset and duration of each episode.

Study staff and the site or co-investigator will record all reportable events with start dates occurring any time after informed consent is obtained until 7 (for non-serious AEs) or 15 days (for SAEs) after the last day of study participation.

During each follow up contact made, the investigator/study staff will inquire about the occurrence of AE/SAEs since the last contact (via telephone or email). Events will be followed for outcome information until resolution or stabilization.

As listed in section 1.3 Schedule of Activities, Adverse Events will be assessed via telephone or email contact with the caregiver 24, 48, and 168 hours after enrollment in the study. Possible Adverse Events will be assessed using open-ended feedback questions on the follow-up questionnaires. Trained research study staff will review the response provided by the caregiver and will follow up by telephone as soon as possible. Details regarding the event will be obtained via telephone and contact will be made daily, or weekly, as required to obtain the resolution/stabilization details.

---

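### The general adverse-event tables are cut off at discharge, before almost all home dosing begins, so on-treatment events such as headache, constipation and flushing would be left out

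*Combined protocol and SAP*

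**What the plan says.** Section 9.4.4 (Safety Analyses) plans incidence, intensity and relatedness summaries by MedDRA System Organ Class and Preferred Term, and treats the occurrence of any AE as a yes/no outcome. The events to be counted are fixed by one sentence: "All AEs beginning after randomization but before discharge will be included". The same section says that the safety outcomes come from "participant follow-up questionnaires performed 24, 48, and 168 hours (7 days) after enrollment".

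Other sections describe exposure and collection:

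- Section 1.3, footnote a: "First dose of study intervention can be administered 8 hours after administration of clinical dose of Ondansetron".
- Section 1.3, footnote b: "Dose of study intervention will be administered at home based on caregiver determination".
- Section 6.4: caregivers may dose "for 48 hours after discharge from the ED, as they feel their child requires the intervention".
- Section 8.3.4: reportable events are defined by "start dates occurring any time after informed consent is obtained until 7 (for non-serious AEs) or 15 days (for SAEs) after the last day", where the day meant is the child's final day in the study.
- Section 9.3: the safety population consists of participants who took any study medication, and it is the population for the AE analysis.

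**The concern.** The tabulation window opens at randomisation, in the ED, and closes at discharge. Study drug is meant to be taken after the family has gone home. If discharge is ED discharge, the tables would compare the arms over a period in which hardly any child has received the randomised treatment. An event caused by a home dose would be collected, coded and then left out.

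The events at stake are the ones that Section 8.3.3.3 names as the most common reactions to the drug: headache, constipation and flushing. Section 2.3.3 gives headache and constipation as examples of what the follow-up contacts should pick up. None of the three is on the list of separately analysed safety outcomes, so the general AE tables and the any-AE outcome are their only planned analysis.

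**Working it through.** The plan states no figure to reproduce. The check compares the tabulation window with the dosing and collection windows.

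**1. What *discharge* means.** The synopsis and Sections 6.4 and 9.1 all use the word for leaving the ED. Section 8.1 (Chart Review) lists discharge date and time among the fields taken from the ED record at enrolment, so a programmer applying Section 9.4.4 would most naturally use that field. The end of a child's participation is worded differently: Section 4.4 speaks of completing the study, and Section 8.3.4 of the last day of participation. No section defines a discharge from the study.

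**2. Overlap with dosing.** Measure time from the clinical ED dose.

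- Earliest study dose: 8 hours (Synopsis; Section 1.3, footnote a).
- End of dosing: 48 hours (Section 1.3, footnote b). Section 6.4 counts 48 hours from ED discharge instead, which moves the end later and does not increase the overlap.
- Length of the dosing period: 48 − 8 = 40 hours.
- Discharge at *h* hours. The documents give no ED length of stay, so *h* = 1 to 8 is an assumption.

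Share of the dosing period inside the AE window = max(0, *h* − 8) / 40.

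| Discharge *h* (hours) | Gap to earliest dose, 8 − *h* (hours) | Share of dosing period covered | Share of 168-hour follow-up, *h*/168 |
|---|---|---|---|
| 1 | 7 | 0% | 0.6% |
| 2 | 6 | 0% | 1.2% |
| 4 | 4 | 0% | 2.4% |
| 6 | 2 | 0% | 3.6% |
| 8 | 0 | 0% | 4.8% |

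The last column is an upper limit. Under Section 5.5 families are approached only after the clinical dose, so the window opens at randomisation, later than time zero. A longer stay would give some overlap: at *h* = 12, for instance, (12 − 8)/40 = 10%.

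**3. Against collection.** Section 8.3.4 records events from consent to 7 days (non-serious) or 15 days (serious) after the last day of participation. If that last day is Day 7, collection runs to about 7 + 7 = 14 days and 7 + 15 = 22 days. The 24, 48 and 168 hour questionnaires all fall after discharge for any child who leaves the ED within the first day. The table rule would discard nearly the whole of that period.

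**4. Against the safety population.** Section 9.3 selects children because they took a dose. Section 9.4.4 would then count only events that, for nearly all of them, began before that dose. The two rules do not fit together.

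**5. What is and is not affected.** Sections 3 and 9.4.4 list seven safety outcomes: diarrhea frequency over 48 hours, maximal diarrhea in 24 hours, SAEs, palpitations, pre-syncope or syncope, chest pain and arrhythmias. Each has its own analysis entry based on the follow-up questionnaires, and diarrhea frequency is explicitly tied to the 48 hours after ED disposition. SAEs are the uncertain item: Section 9.4.4 also says that SAEs and deaths are reported separately but along the same lines as the general AE reports, which leaves open whether they inherit the cut-off.

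No other section gives a different window for the general AE tables.

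**The case against.** The best reply is that this is a drafting slip and not a decision to exclude on-treatment events. The sentence says what will be included and does not contain the word *only*. The same section relies on questionnaires up to 168 hours, and Section 8.3.4 collects onset dates well past discharge. That may well be the intent, but the documents do not say so. A sentence with a start and an end point has no purpose if events outside those points are also counted.

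The second reply is that *discharge* is unqualified. Section 9.4.4 elsewhere calls leaving the ED disposition, and Section 8.1 also uses discharge in connection with revisit diagnoses. Section 9.4.2 allows for children admitted directly from the index visit, some for more than 48 hours; if hospital discharge is meant, their window could span the dosing period. Section 8.2 (Vital Signs) also contemplates study medication before leaving the ED. This stands as a limit: the overlap is close to zero, not exactly zero. It does not rescue the rule for children sent home from the ED, who are the population the trial describes.

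Third, the general tables are descriptive. No test is named for them, the monitoring board may ask for more detail, and collection is untouched, so the omission can be reversed. Section 8.3.5 also keeps common illness symptoms out of standard AE reporting, which narrows what these tables contain. All of that is correct and limits the damage.

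A reader might infer that the trial therefore cannot meet its safety objective. The documents do not support that. Every endpoint that Table 1.0 lists for the objective has its own analysis, and revisits, which the objective gives as an example, are a secondary outcome over 7 days.

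**Conclusion.** The sentence is wrong as written. With *discharge* read as ED discharge, and with discharge 1 to 8 hours after the clinical dose (assumed), the general AE tables cover 0% of the 8 to 48 hour dosing period and at most 4.8% of follow-up. They and the any-AE outcome would omit on-treatment headache, constipation and flushing. The separately listed diarrhea, palpitation, syncope, chest pain and arrhythmia outcomes are not affected. The position of SAEs is unclear.

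The number of events lost cannot be stated. A reader might take it as nearly all AEs in 1030 children, but 1030 is the number to be randomised. The safety population is the unstated number who take a dose, Section 6.4 treats zero doses as compliant, and no AE rate is given. Nor does it follow that the tables must show no difference whatever the truth: some children may be dosed before discharge, and the summaries carry no formal comparison. The conclusion is limited to the tabulation window. It changes no sample size or power figure.

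**What to change.** In Section 9.4.4, replace the sentence with: *All AEs with onset after randomisation through the end of the AE collection period in section 8.3.4 will be included.* Add that the same rule applies to the SAE summaries.

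Events before the first study dose may be shown separately where the time of that dose is available. This should stay optional. Section 8.2 says that the questionnaires prompt for the most recent dose time and Section 7.1 asks for the last. Section 1.3 mentions dose details and Section 6.2.4 a dose tracking form, but no section states that first-dose time is recorded.

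The cost is a sentence or two of plan wording, best settled before database lock. The AE onset dates needed are already to be collected under Section 8.3.4, so no new data are required.

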**Return visits for unscheduled care** to a health care provider related to vomiting, diarrhea, dehydration, fever, abdominal pain, or fluid refusal within 7 days, not including scheduled visits (e.g. reassessments, vaccinations), will also be measured using follow up questionnaires 24, 48, and 168 hours (7 days) after Time 0. Questionnaires will ask caregivers if they brought their child to a health care provider for an unscheduled visit related to the current illness. If a return visit occurred, further questions will be asked related to **Intravenous (IV) insertion**, treatment course, and disposition. Return to care data will be confirmed by reviewing the participant's hospital chart, where

possible. This outcome is important as > 50% of children have a follow-up office visit, 8-18% require an ED visit, and 5-8% are hospitalized.

A **5-point Likert scale will be used to determine caregiver satisfaction** with the therapy provided (ondansetron or placebo oral solution) in the 48 hours following Enrollment in the study.

The following **secondary safety endpoints** are important as they will add more information about the secondary objective. The safety endpoints will include:

- 1) Serious Adverse Events (SAEs)
- 2) Frequency of diarrheal episodes during the 48-hours following ED disposition
- 3) Maximal number of diarrheal episodes in 24 hours
- 4) Palpitations
- 5) Pre-syncope/syncope
- 6) Chest Pain
- 7) Arrhythmias

All safety end point data will be obtained via participant follow-up questionnaires performed 24, 48, and 168 hours (7 days) after enrollment (Time 0). **Frequency and maximal number of diarrheal episodes** will be obtained by asking about presence of diarrhea on each questionnaire the caregiver completes. If diarrhea is present, further questions related to number of episodes will be asked. To obtain SAE and palpitation data, each questionnaire will contain open ended, non-symptom specific questions where caregivers can provide the study team with information about their child's illness or any other concerns they may have. Any response provided to this question will result in a trained study team member discussing the information provided in more detail via telephone. Any symptom or condition noted that meets the definition of an SAE (see Section 8.3.2) will be reported as outlined in Section 8.3.6.

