## 8.2 SAFETY AND OTHER ASSESSMENTS

The following assessments will be performed to ensure the safety of patients as they participate in the study and to assess safety endpoints as described below:

- Frequency and maximal number of diarrheal episodes during the 48 hours following randomization
- Palpitations
- Syncope
- Chest pain

- Arrhythmias
- Serious Adverse Events

Please reference Section 1.3 SoA for a list of all study events/visits.

If caregivers report any symptoms of concern to the research team (palpitations, arrhythmias, syncope, etc.) or are concerned about their child's health, they will be advised to follow up with their health care provider or seek immediate medical attention at the nearest hospital. Caregivers will be provided with a list of possible reasons to seek medical care and a disclaimer regarding symptoms of concern and the required action will be included on all follow-up questionnaires.

**Screening:** A detailed review of the patient's medical history related to the eligibility criteria (e.g. history of prolonged QT syndrome, currently taking apo morphine, etc.) will be performed by the qualified research team member with the caregiver. The information will then be confirmed by the treating physician to comply with medical oversight and ensure patient safety. We will rely on caregiver report of current medications and the medical history of the patient to assess eligibility.

**Baseline/Enrollment Visit – Review of Systems:** After the patient is deemed eligible and has consented to participate in the study, a review of systems will be performed by the qualified research team member to obtain baseline health information prior to starting the study intervention. The research team member will ask the caregiver/participant questions related to the participant's general health by system (e.g. cardiovascular, respiratory, musculoskeletal, etc.). This allows the research team to more accurately measure any new symptoms or conditions that occur after enrollment in the study. During the review of systems, the research team will also ask the caregiver/participant if they are currently taking any medications or supplements. This information will be recorded on study case report forms. This process will take place after the clinical dose of ondansetron is administered however it must be completed prior to the participant taking the first dose of study medication.

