## 7. Arrhythmias

Serious Adverse Events/Deaths will be reported separately in a similar fashion to the more general AE reports. In addition, narratives will be available for each event.

The analysis of safety outcomes will be undertaken as detailed below:

1. **Frequency of diarrheal episodes during the 48-hours following ED disposition:** The total number of episodes of diarrhea related to the presenting illness will be compared between groups (active and placebo) using a generalized linear model to compare differences between Poisson rates whilst adjusting for stratification.
2. **Maximal number of diarrheal episodes in 24 hours:** To test whether this outcome differs between the active and placebo treatments, we will use a Mann-Whitney U-test.
3. **Serious Adverse Events (SAEs):** The frequency of SAEs will be reported for both active and placebo groups. No formal testing will be undertaken.
4. **Palpitations:** The frequency of palpitations will be reported for both active and placebo groups. No formal testing will be undertaken.
5. **Pre-syncope /syncope:** The frequency of pre-syncope/syncope will be reported for both active and placebo groups. No formal testing will be undertaken.
6. **Chest Pain:** The frequency of chest pain will be reported for both active and placebo groups. No formal testing will be undertaken.
7. **Arrhythmias:** The frequency of arrhythmias will be reported for both active and placebo groups. No formal testing will be undertaken

---

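### Four cardiac-type safety endpoints have no symptom-specific question, so their absolute frequencies are likely under-ascertained and zero counts will not be evidence of absence

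*Combined protocol and SAP*

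**What the plan says.** Section 3 and Table 1.0 list palpitations, pre-syncope/syncope, chest pain and arrhythmias as safety endpoints, next to serious adverse events and two diarrhea measures.

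Section 9.4.4 gives the data source for all four, and for serious adverse events: "each questionnaire will contain open ended, non-symptom specific questions where caregivers can provide the study team with information". What follows depends on the caregiver writing or saying something: "Any response to this question will result in a trained study team member discussing the information provided in more detail via telephone". Section 3 describes the same method but names fewer events: "To obtain SAE and palpitation data, each questionnaire will contain open ended, non-symptom specific questions". Section 8.3.4 applies it to adverse events generally: "Possible Adverse Events will be assessed using open-ended feedback questions on the follow-up questionnaires".

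Diarrhea is handled differently. Its presence is asked about on every questionnaire, and episode counts follow if the answer is positive (Sections 3 and 9.4.4).

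The analysis is descriptive. Section 9.4.4 says "The frequency of palpitations will be reported for both active and placebo groups", makes the same statement for the other three, and plans no formal test.

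**The concern.** A safety endpoint reported as a frequency needs a numerator that was looked for. Here a blank answer can mean that no event occurred or that the caregiver did not mention one, and the form cannot tell these apart. Mild or transient episodes are the easiest to leave out, particularly when a caregiver reports for a young child on a web form. An event that nobody volunteers is not recorded, so the likely direction is under-counting.

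The collection standard is also uneven. Diarrhea is solicited and the four cardiac-type symptoms are volunteered, yet both appear in one list of safety outcomes. At baseline, Section 8.2 goes through the child's health by body system, cardiovascular included, so that new symptoms can be measured more accurately. No matching step is described after dosing.

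At stake is how a row of zeros or near-zeros would be read: as the absence of a signal, when the form did not ask.

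**Working it through.** **Step 1. Does any other route ask about these symptoms by name?**

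- Section 3, questionnaire content: includes a general enquiry about side effects, with further questions on the telephone after a positive answer. No cardiac symptom is listed.
- Section 8.3.4, staff enquiry about adverse events at each contact, by telephone or email: general, and the same section says that the assessment uses open-ended feedback questions.
- Section 8.3.4, return to care or monitor review: covers return to the enrolling ED only, and review of data already collected.
- Section 8.2, "a disclaimer regarding symptoms of concern and the required action will be included on all follow-up questionnaires": this may prompt recall, but it advises on seeking care and records no answer.
- Section 8.1, chart review: limited to revisits for the current illness, which Section 3 defines by gastrointestinal, fever and fluid-intake complaints. A visit for fainting or palpitations alone falls outside that scope.

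None contains a symptom-specific item, and the schedule in Section 1.3 includes no ECG.

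**Step 2. Denominators.** The plan states no expected frequency or capture rate for these endpoints, so the only plan figure to reproduce is the sample size. The pooled two-proportion formula for 30% versus 20%, two-sided 0.05 and 90% power gives 392 per arm, or 784, as stated in Section 9.2. Then 784/0.90 = 871.1 (stated 870) and 870/0.92² = 1027.9 (stated 1030). With 1:1 allocation, 1030/2 = 515 per arm. After the plan's 10% loss to follow-up, 515 × 0.90 = 463.5, taken as 463.

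**Step 3. What a zero count would rule out.** Let s be the share of true events that is reported. The documents give no value, so s is assumed over a range. With zero reports among n children, the one-sided 95% upper limit on the reported rate is U = 1 − 0.05^(1/n), and on the true rate it is U/s.

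| Assumed capture s | n = 515 | n = 463 |
|---|---|---|
| 1.00 | 0.58% | 0.64% |
| 0.75 | 0.77% | 0.86% |
| 0.50 | 1.16% | 1.29% |
| 0.25 | 2.32% | 2.58% |

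The two-sided 95% limit for 0/515 under full capture is 0.71%. The safety population in Section 9.3 counts only children who took a dose, so the real denominators will be smaller and the bounds wider.

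For an assumed true rate of 1%, expected reports per arm are 515 × 0.01 × s = 5.2, 3.9, 2.6 and 1.3 at the four values of s.

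**Step 4. Between-arm comparison.** If s is equal in both arms, the reported difference is s × (p1 − p0) and the reported ratio is (s × p1)/(s × p0) = p1/p0. For assumed true rates of 3% and 1%, the difference falls from 2.0 points to 1.5, 1.0 and 0.5 at s = 0.75, 0.50 and 0.25. The ratio stays at 3.

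**Step 5. Arrhythmia.** Section 2.3.1 cites 0.003% for ventricular arrhythmia within 24 hours. Expected events per arm are 515 × 0.00003 = 0.015 under perfect capture. A zero is all but certain and says little whichever way the question is put.

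**The case against.** The strongest reply is that the open question is not the whole system. Side effects are asked about, staff enquire about adverse events, caregivers see a list of warning symptoms, and events can surface at the enrolling ED or through monitoring. A reader might infer that these symptoms are collected through the open question alone. Step 1 shows that the documents do not support that. The reply stands to this extent: the other routes soften the gap, but being general they do not close it.

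Second, the endpoints are descriptive, no test is planned, and blinding favours equal capture in the two arms. This also stands. The ratio need not be biased; the weakness lies in the absolute frequencies and the absolute difference.

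Third, a yes/no item cannot make a preverbal child's palpitations or chest pain visible to a caregiver. That is correct and limits the gain in the youngest children. Fainting remains observable, and older children can report the rest. The documents give no age mix, so the size of this limit is unknown.

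Fourth, a reader might extend the point to headache and constipation, which Section 8.3.3.3 calls common. Section 2.3.3 already names both as targets of the follow-up contacts, so that extension is weak.

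**Conclusion.** The point holds as one of ascertainment. The plan names four safety endpoints, describes no question that asks about them, and commits to reporting their frequencies. For palpitations, pre-syncope/syncope and chest pain, counts are likely to fall short of the truth by an unknown amount, and a low or zero count should not be read as evidence of absence. As an illustration, 0/515 is compatible with a true rate of up to 0.58% under full capture and up to about 1.2% or 2.3% at 50% or 25% capture (one-sided 95%). These capture rates are assumptions. Arrhythmia stands apart: it is too rare for any questionnaire to inform.

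A reader might conclude that the frequencies are certain to be falsely reassuring, or that the safety objective cannot be answered. The documents support neither. They give no capture rate, so the direction is reasonable but the size cannot be fixed. The safety objective in Table 1.0 gives diarrhea and revisits as its examples, and both are asked about directly. The primary analysis is unaffected. This is a correctable measurement gap that should be addressed.

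**What to change.** On the existing 24, 48 and 168 hour questionnaires, add one direct yes/no item each for palpitations or a racing heart, fainting or near-fainting, chest pain, and a rhythm problem diagnosed by a clinician. Keep the open question for everything else, and use the existing call-back for any positive answer. Items for headache and constipation are optional.

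In Section 9.4.4, report solicited and spontaneous events separately, by arm and by form version, with exact confidence intervals. Label counts from the current form as spontaneously reported and as a lower bound. That labelling needs no change to the form and is worth doing even if the form stays as it is.

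The cost is modest but real. The Statement of Compliance requires REB review and approval before such a change, so notification would not be enough, and there are six sites. Direct items will draw some background positive answers and extra call-backs, expected equally in both blinded arms. The version 4.0 rationale in Section 10.4 speaks of continuing recruitment, so ascertainment would change mid-trial, which is why results should be split by form version. The gain will be limited in preverbal children.
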